#### Objective and study sample

We will assess Veterans’ perspectives about their experiences with care coordination, integration with other healthcare services, and perceived health impacts. We will sample and recruit participants from among Veterans identified in Aim 1 from FY2021 and based at VA sites with active care coordination programs (29 sites). Initially approved for a sample of 2,500 Veterans, we will invite participants from the selected sites and using a proportionate random sample of those with and without care coordination services.

#### Measures

Measures will be drawn from an adaptation of Singer's Framework for Measuring Integrated Patient Care (32) and the Patient Perceptions of Integrated Veteran Care (PPIC 2.1) survey instrument (44), which has been validated and psychometrically tested to collect information on patients’ care coordination experiences.

The PPIC 2.1 survey includes items organized under six dimensions of integrated patient care including: (1) *staff knowledge* about the patient’s medical history (3-item dimension), (2) *provider support for the patient*’*s self-directed care* (5-item dimension), (3) *test result communication* (3-item dimension), (4) *provider knowledge* of the patient (5-item dimension), (5) *provider support for medication adherence and home health management* (4-item dimension) and (6) *specialist knowledge* about the patient’s medical history (2-item dimension) (Table 2).

**Table 2 T2:** PPIC 2.1 survey dimensions and sample questions.

Survey dimension	Sample question
Staff knowledge	In the past 6 months, how often did these other staff seem up-to-date about the care you were receiving from this provider?
Provider support for self-directed care	In the past 6 months, did this provider or someone in his or her office ask you about these things that make it hard for you to take care of your health, and did you and this provider or someone in his or her office come up with a plan to help you deal with things that make it hard for you to take care of your health?
Test result communication	In the past 6 months, how often were your test results presented in a way that was easy to understand?
Provider knowledge	How would you rate this provider's knowledge of your values and beliefs that are important to your health care?
Provider support for medication adherence and home health management	In the past 6 months, how often did this provider or someone in his or her office talk with you about what to do if you have a bad reaction to your medicine?
Specialist knowledge	When you see this specialist, does he or she seem to know enough information about your medical history?

See Friedberg et al. (44) for a full list of questions under each survey dimension.

Measures for analysis will be constructed from the six dimensions of the validated questionnaire items of the PPIC 2.1. Additional validated items will verify provider attribution, measure potential differences in individual tendency to give more positive or negative responses using the standardized life orientation test-revised (LOT-R) scale (45), and provide information about Veterans’ sociodemographic characteristics. Surveys will be linked with existing VA and CMS data to verify or ascertain Veterans’ sociodemographic characteristics, and to ascertain their clinical characteristics and healthcare use, including use of care coordination services.

To account for clustering by VA site, we considered an intra-class correlation coefficient of 0.01. Previous work by Benzer et al. (46) using an adaptation of the PPIC instrument on a cohort of Veterans reported mean scores [standard deviation (SD)] in the dimensions of: knowledge integration 3.18 (SD 0.83), support for self-care 3.00 (SD 0.85), and staff knowledge 3.02 (SD 0.91). For our target sample size, we have over 96% power to detect a significant difference between group means as low as 0.3, assuming a maximum SD of 0.9. Power analyses used alpha = 0.05 and were conducted in PASS v16.0.5.62 (47).

#### Analysis

In descriptive analyses, we will compare mean scores for the six survey dimensions between Veterans with and without care coordination services. For individual survey items, we will also compare proportions of the sample of Veterans who reported the most positive rating (top-box score). Next, we plan to estimate six GLMMs, one for each of the six survey dimensions. We will compare mean dimension scores among Veterans with and without care coordination services, adjusting for Veterans’ sociodemographic and clinical characteristics, clustering at the VA facility level, and Veterans’ tendency to give more positive or negative responses using the LOT-R.

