#### Objective and study sample

We will characterize and compare the relationship between receiving care coordination services and subsequent healthcare use, health outcomes, and healthcare costs among Veterans with high-risk, high-need conditions in a prospective observational study. With existing data available in the VA's electronic health record (EHR), VA-purchased care claims, and Medicare claims data from the Centers for Medicare and Medicaid Services (CMS), we will identify and match Veterans with complex care needs with and without care coordination services based on clinical and sociodemographic characteristics and prior healthcare use. The VA lacks a standardized care needs assessment in the EHR, but does include a means to identify Veterans with high risk for hospitalization and/or mortality, based on annual care assessment of needs (CAN) scores (33). Those with a CAN score of 85 or greater, indicating their predicted probability for hospitalization and/or mortality at one-year is at or above the 85th percentile, will be included. The CAN score is generated from VA EHR data and includes information on sociodemographic characteristics, chronic illness measures (including the Deyo-Charlson comorbidity index), VA healthcare use, vital sign parameters, laboratory test values, specific medication use, and 18 drug interactions. The CAN score has been well validated for predicting hospitalization and mortality and is in wide use in the VA. Use of the CAN score allows us to identify those most likely to benefit from care coordination and explore the relationships with processes and outcomes. Exclusion criteria include CAN score less than 85 and missing data for key variables required for matching. We will follow Veterans with complex care needs, with and without care coordination services over time to examine and compare their healthcare use, costs, and health outcomes.

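### The stated adjustment set for the six Aim 2 models leaves out prior healthcare use, which Aim 1 matches on for the same comparison and which may confound the perceived-integration scores

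*Protocol article*

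**What the plan says.** **Aim 1, Objective and study sample.** The study will identify and "match Veterans with complex care needs with and without care coordination services based on clinical and sociodemographic characteristics and prior healthcare use". Entry requires a CAN score of 85 or more, and VA healthcare use is one of the inputs to that score.

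**Table 1.** The codes that define receipt of care coordination include two transitional care management codes, 99495 and 99496, both tied to a hospital discharge. The other codes (chronic care management, complex chronic care management, case management) are not.

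**Aim 2, Objective and study sample.** Participants come "from among Veterans identified in Aim 1 from FY2021", "using a proportionate random sample of those with and without care coordination services", at 29 sites. The size is given as "Initially approved for a sample of 2,500 Veterans". The number expected to respond and the split between groups are not given.

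**Aim 2, Measures.** Surveys are linked to VA and CMS data "to ascertain their clinical characteristics and healthcare use, including use of care coordination services".

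**Aim 2, Analysis.** Six GLMMs, one per PPIC dimension, compare mean scores with adjustment for "sociodemographic and clinical characteristics, clustering at the VA facility level", and for "tendency to give more positive or negative responses using the LOT-R". Healthcare use is not in this list.

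**The concern.** Both aims contrast Veterans who did and did not receive care coordination. For Aim 1 the authors name three classes of variable on which the groups should be comparable. The Aim 2 list carries over two of them and adds LOT-R. The third, prior use, does not appear, although the study already needs it for Aim 1 and links healthcare use to the surveys.

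Prior use could plausibly confound Aim 2. Exposure through a transitional care code implies a recent hospital stay, so at least part of the exposed group is selected on use. The outcomes are ratings of contact with care: whether staff seemed up to date, whether test results were clear, what the specialist knew. It is reasonable to expect that the amount of earlier contact affects such ratings, upward or downward. If so, part of a difference between groups in any of the six dimensions could reflect how much care Veterans had used before, and not the coordination service.

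**Working it through.** **1. Can healthcare use be read into clinical characteristics?** Not readily. The Aim 1 matching sentence and the Aim 2 linkage sentence each list the two as separate items.

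**2. Is it handled elsewhere in Aim 2?** Partly, at most. The CAN cut-off narrows differences in VA use, but Veterans above it can still differ. Only VA use is named as a CAN input, and CAN is not named as an Aim 2 covariate. Sampling from Veterans identified in Aim 1 could carry over some balance if the frame is the matched cohort. The article does not say that it is, and non-response can undo balance in any case.

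**3. The plan's own power figure.** The article states over 96% power for a difference of 0.3 with SD 0.9, ICC 0.01 and alpha 0.05 (taken as two-sided). The analysed number and group split are not given, so the figure cannot be reproduced exactly. With equal groups and N analysed over 29 sites:

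- Design effect: DE = 1 + (N/29 − 1) × 0.01
- Standard error: SE = 0.9 × √(4 × DE / N)
- At N = 592: DE = 1.194, SE = 0.081, power 96.0%
- At N = 2,500: DE = 1.852, SE = 0.049, power above 99.9%

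The stated power is therefore attainable from about 592 analysed Veterans upward. This point does not dispute it.

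**4. Illustration of bias.** Two inputs are assumptions that the documents do not supply: the standardized group difference in prior use that remains after the stated covariates (d), and the partial effect of prior use on a dimension score, in SD per SD (b).

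- Bias = d × b × 0.9
- False-positive rate = P(|Z + bias/SE| > 1.96)

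The SE is taken without a design effect and with the full one. The first rate or ratio in each cell is without, the second with.

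| d, b (assumed) | Bias (points) | Bias/SE, N = 590 (SE 0.074; 0.081) | False-positive rate, N = 590 | Bias/SE, N = 2,500 (SE 0.036; 0.049) | False-positive rate, N = 2,500 |
|---|---|---|---|---|---|
| 0.2, 0.1 | 0.018 | 0.24; 0.22 | 5.7%; 5.6% | 0.50; 0.37 | 7.9%; 6.6% |
| 0.3, 0.2 | 0.054 | 0.73; 0.67 | 11.3%; 10.2% | 1.50; 1.10 | 32.3%; 19.7% |
| 0.5, 0.2 | 0.090 | 1.21; 1.11 | 22.9%; 19.9% | 2.50; 1.84 | 70.5%; 45.1% |

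Against the 0.3-point target, the middle row is 0.054/0.3 = 18% and the last row 0.090/0.3 = 30%. The bias in points does not depend on N. The false-positive rate rises with N because the SE shrinks.

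**The case against.** The strongest reply is that the article contradicts nothing. Aim 1 studies ED and urgent care visits, hospitalizations, costs and mortality, where prior use is close to a baseline value of the outcome. Aim 2 studies perceptions, for which a different set of covariates can be defended. The Aim 2 sentence names categories only, and a condensed article may leave individual covariates to a fuller plan. This stands so far as it goes: a reader might infer that one comparability rule is stated in two incompatible ways, but no passage lays down a single rule for both aims. What remains is that the Aim 2 sentence is specific enough to name LOT-R, and an analyst following it would leave prior use out.

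Three other stronger readings should also be resisted.

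- **That the Aim 2 sample is not drawn from matched pairs.** The article is silent on this. The matched cohort may be the frame.
- **That healthcare use is linked and then unused.** The linkage also supplies receipt of care coordination, which every Aim 2 model needs. Only the remaining use data have no stated role in the models.
- **That care coordination in general goes to heavy users.** Only the transitional care codes show this by definition.

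It is also fair to say that the Discussion limits the study to associations. That affects how results are worded, but it is not a reason to omit a measured confounder that the study controls in its other quantitative aim.

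**Conclusion.** The point holds as an avoidable gap in the stated Aim 2 adjustment, affecting all six models. It is not a contradiction, nor a demonstrated bias. The omission and the availability of the data are plain in the text. That prior use differs between groups is supported by the transitional care codes for part of the exposed group. That it affects PPIC scores is plausible but not documented.

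The size is illustrative only. At the mid-range assumptions the bias is about 0.05 points, with a false-positive rate of about 10-11% at roughly 590 respondents and 20-32% at 2,500. A reader might take the 70% cell as the headline. The documents do not support that: it needs the most extreme assumed inputs, no design effect, and a response from all 2,500, a number given only as the approved sample. The direction of any bias is unknown, and the CAN rule or carry-over of matching could make it smaller.

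**What to change.** In the Aim 2 Analysis section, add to all six GLMMs the same prior healthcare-use variables that are used for Aim 1 matching. Use the same look-back period and the same index date for comparators, and measure use before the first care coordination service. The timing matters because use after the service starts may be a consequence of it, and adjusting for that could remove part of the effect of interest. The article gives no index date for Veterans without care coordination, but matching on prior use in Aim 1 already requires one, so Aim 2 can adopt it.

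In the Aim 2 Objective and study sample section, state whether the sample is drawn from the Aim 1 matched set and whether the matching is kept in the analysis.

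The cost is a few extra model terms and a sentence of text. The variables have to be built for Aim 1 anyway, and no change to sample size or data collection follows.

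### The Aim 2 models and power input recognise clustering by facility only, although most sample survey questions are anchored to one provider and provider attribution is verified

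*Protocol article*

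**What the plan says.** Under Aim 2, Analysis, the article states: "we plan to estimate six GLMMs, one for each of the six survey dimensions". The models compare mean dimension scores with and without care coordination. They adjust for sociodemographic and clinical characteristics, "clustering at the VA facility level", and response tendency measured with the LOT-R. Facility is the only clustering level named.

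The power paragraph under Aim 2, Measures, uses the same level: "To account for clustering by VA site, we considered an intra-class correlation coefficient of 0.01". It concludes that "we have over 96% power to detect a significant difference between group means as low as 0.3, assuming a maximum SD of 0.9".

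The same section describes what the scores measure. Of the six sample questions in Table 2, four refer to a particular provider, for example "how often did this provider or someone in his or her office talk with you about what to do". A fifth refers to a particular specialist, and the test-results question names no clinician. Three of the six dimensions are provider dimensions by name, with 5 + 5 + 4 = 14 of the 22 items. The section adds: "Additional validated items will verify provider attribution".

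**The concern.** Two Veterans who rate the same provider share that provider's way of working, so their scores are likely to be correlated beyond what they share by attending the same facility. A facility random intercept cannot absorb differences among providers within a facility. The models adjust for the rater's tendency (LOT-R) but not for who is rated.

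Two separate consequences could follow.

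- **Precision.** If receipt of care coordination also clusters by provider, the standard error of the with/without contrast is too small. Table 1 makes this plausible, since it lists services delivered by a practitioner and, for some codes, their clinical staff. It does not establish it.
- **Confounding.** If providers who give more integrated care also use care coordination more, a facility-only model credits some of their practice to the service. The bias runs in the direction of the Aim 2 hypothesis, and a larger sample does not reduce it.

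**Working it through.** **Inputs from the article:** 29 sites, a sample of 2,500 (about 86 per site), SD 0.9, target difference 0.3, site ICC 0.01, alpha 0.05 (taken as two-sided).

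**Not in the article, so assumed:** respondents per provider (m), provider ICC (ρ_y), within-provider correlation of receipt (ρ_x), the correlation between provider quality and use of care coordination, the number of completed surveys, and a 1:1 split.

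**1. The plan's own power figure.** With 2,500 respondents split 1:1 and no design effect, SE = 0.9 × √(4/2500) = 0.036. Then 0.3/0.036 = 8.3, so power exceeds 99.9%. The full site design effect is 1 + (86.2 − 1) × 0.01 = 1.85, and power is still above 99.9%. The bound of 96% is met. Its exact value cannot be reproduced without the number of completed surveys and the split; 96% corresponds to about 496 completes with no design effect, or 592 with the full site effect.

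**2. Power with a provider level added.** In the worst case (ρ_x = 1), the design effect gains (m − 1)ρ_y. With m = 10 and ρ_y = 0.10 it is 1.852 + 0.90 = 2.752. Then SE = 0.036 × √2.752 = 0.0597, 0.3/0.0597 = 5.02, and power is 99.9%. With ρ_y = 0.20 the design effect is 3.652 and power is 99.2%. With 1,000 completes, the range from (m = 2, ρ_y = 0.05) to (m = 10, ρ_y = 0.10) is 99.4% to 94.1%. With 750 completes it is 98.0% to 87.6%.

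**3. Understated standard errors, no confounding.** The variance is understated by 1 + (m − 1)ρ_y ρ_x, and the SE by its square root. The true two-sided level is then 2[1 − Φ(1.96/√that factor)].

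| m | ρ_y | ρ_x | variance factor | SE factor | true type I error |
|---|---|---|---|---|---|
| 2 | 0.05 | 0.5 | 1.025 | 1.01 | 5.3% |
| 2 | 0.10 | 0.5 | 1.05 | 1.03 | 5.6% |
| 5 | 0.10 | 0.5 | 1.20 | 1.10 | 7.4% |
| 10 | 0.10 | 0.5 | 1.45 | 1.20 | 10.4% |
| any | any | 0 | 1.00 | 1.00 | 5.0% |

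Simulations used 29 sites, a site intercept only, ρ_y = 0.10 and a correlation of 0.5 on the latent scale of receipt. They gave about 5-6% at 2-5 respondents per provider, about 8% at 8-9 and 9% at 10. They run lower than the table because, at 50% receipt, a latent correlation of 0.5 is a correlation of (2/π) × arcsin(0.5) = 0.33 between the yes/no indicators. Using 0.33 at m = 10 gives 1 + 9 × 0.10 × 0.33 = 1.30, and a true level of 8.6%. A provider intercept nested within facility returned the simulated rate to about 5%.

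**4. Confounding.** The provider SD is 0.9 × √0.10 = 0.285. Assume a correlation of 0.3 between provider quality and the provider's component of receipt, which is half the latent variance, with 50% receipt. The expected false difference is 0.285 × 0.3 × √0.5 × 2 × 0.798 = 0.096. Simulations with no true effect agree:

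- Facility intercept only: 0.09-0.10, which is 30% or a little more of the 0.3 target. The false-positive rate was 36% at 5 respondents per provider and 73% at 10, the latter with a larger total sample.
- Adding a nested provider intercept (10 providers per site, 4 respondents each): about 0.08 remains.
- Adding the provider's share of patients with care coordination as a covariate: below 0.01.

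**The case against.** A condensed article commonly leaves lower-level random effects and the standard-error method to an analysis plan that is not shown. Facility-level cluster-robust standard errors would largely cover providers nested in a facility (simulated false positives about 5-7% without confounding). This has some force, but the article does name the clustering level in both the model and the power input, and stops at facility in both. It does not mention robust errors, and these would not touch confounding.

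Every size above also rests on inputs the article does not give, and nothing says that the rated provider delivers the coordination. Table 1 includes post-discharge and case management services, and nurses and social workers take part. This stands, and it is why the point is conditional.

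The study states under its limitations that it describes associations, not causal effects. That is fair, and it is why a within-provider contrast should not replace the primary one: if coordination works at team level, conditioning on the provider's share removes part of the association being studied.

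Three stronger readings are tempting, and the article does not support them:

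- A reader might infer that most survey scores rate one named provider. Only six of 22 items are shown. Of the four tied to a provider, one rates other staff and two extend to the office.
- A reader might infer that the power claim fails. At 2,500 with a 1:1 split it stays above 99%. It drops below 96% only with far fewer completed surveys and the more extreme provider clustering in step 2.
- A reader might infer that the Aim 2 result will be biased. That needs provider quality to be related to use of care coordination, for which the article gives no evidence either way.

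**Conclusion.** The point holds in a limited form. The planned models leave correlation between respondents who share a provider unmodelled, although the sample questions are largely provider-anchored and attribution is to be verified.

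The effect on standard errors is modest. With a provider ICC of 0.10 and a latent receipt correlation of 0.5, type I error is about 5-6% at 2-5 respondents per provider and 8-9% at 8-10. It is nil if receipt does not cluster by provider.

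Confounding is potentially larger, about 0.09-0.10 against a target of 0.3, but only under the further assumption of a 0.3 correlation between provider quality and use of care coordination. This is a worthwhile and cheap improvement. It does not show that the Aim 2 analysis is invalid.

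**What to change.** In Aim 2, Analysis:

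1. Add a random intercept for provider (or care team) nested within facility to each of the six models where respondents share a provider, using the verified attribution. For the specialist dimension the relevant clinician is the specialist, if that identity is available.
2. Report the number of respondents per provider and the estimated provider ICC, so readers can judge whether the level matters.
3. As a sensitivity analysis beside the primary contrast, fit a within-between model with the provider's share of Veterans receiving care coordination as a covariate. This is needed because the intercept corrects the standard errors but leaves most of any confounding.

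The cost is a few sentences and slightly more complex models. Intervals will be slightly wider, and providers with one respondent will add little to the within-provider term. The within-provider contrast also answers a narrower question than the overall association, and should be labelled so. The sample size need not change on this account.
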